# Displaced midshaft fractures of the clavicle: non-operative treatment versus plate fixation (Sleutel-TRIAL). A multicentre randomised controlled trial

**DOI:** 10.1186/1471-2474-12-196

**Published:** 2011-08-24

## Abstract

**Background:**

The traditional view that the vast majority of midshaft clavicular fractures heal with good functional outcomes following non-operative treatment may be no longer valid for all midshaft clavicular fractures. Recent studies have presented a relatively high incidence of non-union and identified speciic limitations of the shoulder function in subgroups of patients with these injuries.

**Aim:**

A prospective, multicentre randomised controlled trial (RCT) will be conducted in 21 hospitals in the Netherlands, comparing fracture consolidation and shoulder function after either non-operative treatment with a sling or a plate fixation.

**Methods/design:**

A total of 350 patients will be included, between 18 and 60 years of age, with a dislocated midshaft clavicular fracture. The primary outcome is the incidence of non-union, which will be determined with standardised X-rays (Antero-Posterior and 30 degrees caudocephalad view). Secondary outcome will be the functional outcome, measured using the Constant Score. Strength of the shoulder muscles will be measured with a handheld dynamometer (MicroFET2). Furthermore, the health-related Quality of Life score (ShortForm-36) and the Disabilities of Arm, Shoulder and Hand (DASH) Outcome Measure will be monitored as subjective parameters. Data on complications, bone union, cosmetic aspects and use of painkillers will be collected with follow-up questionnaires. The follow-up time will be two years. All patients will be monitored at regular intervals over the subsequent twelve months (two and six weeks, three months and one year). After two years an interview by telephone and a written survey will be performed to evaluate the two-year functional and mechanical outcomes. All data will be analysed on an intention-to-treat basis, using univariate and multivariate analyses.

**Discussion:**

This trial will provide level-1 evidence for the comparison of consolidation and functional outcome between two standardised treatment options for dislocated midshaft clavicular fractures. The gathered data may support the development of a clinical guideline for treatment of clavicular fractures.

**Trial registration:**

Netherlands National Trial Register NTR2399

## Background

### Epidemiology

Fractures of the clavicle account for 2.6 to 4 percent of all adult fractures and 35 percent of all injuries to the shoulder girdle [1,2]. The annual incidence of clavicular fractures is estimated between 29 and 64 per 100,000. Fractures of the middle third (midshaft) account for 69 to 82 percent of all clavicular fractures, whereas distal fractures represent 21 to 28 percent. Medial-end injuries are less common, approximately 2 to 3 percent of all clavicular fractures [2,3]. The average age of patients sustaining a midshaft clavicular fracture is 33 years, 70 percent of the patients is male [4]. A fall or a direct blow to the shoulder, giving an axial compressive force on the clavicle, is the most common trauma mechanism of injury for any clavicular fracture [5-7].

### Current treatment concepts

Midshaft fractures have traditionally been treated non-operatively, even when substantially displaced [8]. The non-operative treatment strategy was based on early reports suggesting that clavicular non-unions are very rare. Clavicular mal-union, if present, was reported as being of radiographic interest only, without clinical importance [9]. Moreover, surgical treatment of acute midshaft fractures was not favoured due to relatively frequent and serious complications such as infection, non-union, pin migration, broken plates, and necessity of removal of hardware [2]. However, the prevalence of non-union or mal-union in dislocated midshaft clavicular fractures after conservative treatment is higher than previously presumed and fixation methods have evolved. Of all midshaft clavicular fractures, about two-thirds end up having some degree of mal-union [5]. Recent studies reported a non-union rate up to 15 percent and more [10,11,4] and a potential 20 to 25 percent decrease in shoulder function and arm strength [4,12,11-17].

The currently described indications for surgical treatment are open fractures, neurovascular involvement, skin compromise and wide separation of bone fragments with soft tissue interposition. Initial clavicular shortening exceeding 20 mm is upcoming as an indication for operative treatment, because shortening caused by dislocation has been associated with potential shoulder dysfunction [18,12]. An associated floating shoulder, or a scapular neck fracture, are relative indications for operative treatment of the clavicular fracture. Non-union and mal-union are mentioned as a delayed indication for operative treatment. If an operation is considered for displaced midshaft clavicular fractures, the preferred method of fixation is reduction and internal fixation by means of wires, pins, or plates with screws.

Valid and scientific evidence showing primary operative intervention to be superior compared to closed treatment for dislocated fractures, still lacks [19,20]. Surgery is accepted more and more as primary treatment for dislocated midshaft clavicular fractures, mainly because the results of non-operative treatment are interpreted as inferior to operative treatment [9,15,21,22]. Several studies have examined the safety and efficacy of primary open reduction and internal fixation (ORIF) for completely displaced midshaft clavicular fractures and have noted a high union rate with a low complication rate [23,24,11,9]. However, all these studies were retrospective and only one recent study prospectively compared locking plate fixation with non-operative treatment [9]. In this multicentre, prospective randomised trial 132 patients with a displaced midshaft clavicular fracture were allocated to either operative treatment with plate fixation (n = 67) or non-operative treatment (n = 65). The investigators concluded that operative treatment results in improved functional outcome and a lower rate of mal-union and non-union compared with non-operative treatment after one year of follow-up [9]. One of the important limitations of this prospective randomised trial was a selective loss to follow-up, which occurred predominantly in the non-operatively treated group. This may have obscured the true difference in the outcome parameters between the study groups.

A cost-effectiveness analysis [4] has been performed in this multicentre, prospective randomised trial [9], showing that the cost-effectiveness of ORIF of displaced midshaft clavicular fractures is dependent on the duration and magnitude of functional benefit after ORIF, the disutility before union and increased time to union associated with non-operative treatment, and the actual cost of treatment.

### Rationale for the trial

A multicentre randomised clinical trial with sufficient power is needed to provide scientific support for a preferred treatment strategy for dislocated midshaft fractures of the clavicle. The aim of this trial is to compare the results of plate fixation with non-operative management of dislocated midshaft fractures of the clavicle with respect to the incidence of non-union, functional outcome, pain scores, Quality of Life, cosmetic aspects, and complications.

## Methods/Design

### Study design

The Sleutel-TRIAL is designed as a multicentre randomised controlled trial. In total twenty-one academic and non-academic centres in the Netherlands will participate. The study started 15 June, 2010. The trial has been developed to meet the Declaration of Helsinki (59^th ^World Medical Association General Assembly, Seoul, October 2008) and in accordance with the Medical Research Involving Human Subjects Act [25]. It will follow the CONSORT (CONsolidation of Standards of Reporting Trials) guidelines [26-28].

### Recruitment, consent and randomisation

All eligible persons presenting at the Emergency Department (ED) or at the outpatient clinic with a new, dislocated midshaft clavicular fracture are informed about this trial. They receive information and a consent form from the attending physician, the physician assistant or the clinical investigator. After written informed consent has been obtained, the patient is randomised for either operative therapy with a plate fixation or for non-operative therapy. Minimisation randomisation is accomplished via the trial website using TenALEA (Trans European Network for Clinical Trials Services), an online registration and randomisation program. All patients are randomly allocated to one of the two treatment arms in a 1:1 ratio in each participating hospital. For each subsequent participant the allocation depends on the included participants to minimise the imbalance [29].

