### Outcome measures

The primary outcome is the incidence of non-union. This is determined objectively on X-rays by an independent radiologist and two surgeons, and subjectively by evaluation of the clavicular and the arm function. The function of the arm is measured with the Constant Score. The Constant score consists of four variables, reflecting both function and pain of the shoulder joint [30,31]. The subjective variables in the Constant Score are pain, activities of daily living and arm positioning. The objective variables are range of motion (ROM) without pain and strength [32]. The arm strength is measured with the MicroFET2 (Micro Force, Evaluating and Testing 2, Hoggan Health Industries Inc, West Jordan, UT, USA), a hand-held dynamometer. This device measures the force a patient can produce against the force of the examiner in Newton (N). All arm movements (i.e., retroflexion, anteflexion, abduction, adduction, endorotation and exorotation) are evaluated six weeks after initial trauma or operation in comparison with the contralateral side and thereafter at each follow-up moment. For all measurements the Make Test is used. The Make Test is characterised by the examiner holding the dynamometer stationary while the subject exerts a maximal force against the dynamometer and the examiner [33]. The results produced with the hand-held dynamometer have been shown to be reproducible, especially when measured by one single examiner at each hospital (intra-rater reliability) [33]. The inter- and intra-rater reliability of hand-held dynamometry varied in the range from good to high [34,35].

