### Statistical analysis

The research data will be reported following the CONsolidated Standards of Reporting Trial (CONSORT) [26-28]. Complication rates and recovery of function of the shoulder will be compared between the two intervention groups using the Chi-squared test. All other endpoints will be compared using co-variate analysis and student's T-test or Mann-Whitney U-test for, respectively, parametric or non-parametric data. Multivariate linear regression analysis will be performed to model the relation between binary outcome variables and treatment, adjusted for covariates. Data will be presented as mean ± SD (Standard Deviation) for parametric data or medians and percentiles (non-parametric data). P-values lower than 0.05 will be considered statistically significant. The data will be analysed using SPSS version 17 or higher (Statistical Package for the Social Sciences Inc, Chicago IL, USA).

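### Allocation is balanced 1:1 within each of 21 hospitals, but the named tests leave hospital out: a small loss of precision for the scores, next to none for non-union

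*Protocol article*

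**What the plan says.** **Allocation.** Recruitment, consent and randomisation describes minimisation through an online system: "All patients are randomly allocated to one of the two treatment arms in a 1:1 ratio in each participating hospital", and "For each subsequent participant the allocation depends on the included participants to minimise the imbalance". Hospital is the only balancing unit named. Study design gives the number of sites: "In total twenty-one academic and non-academic centres in the Netherlands will participate".

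**Analysis.** Statistical analysis assigns the tests by type of endpoint. First: "Complication rates and recovery of function of the shoulder will be compared between the two intervention groups using the Chi-squared test". Then: "All other endpoints will be compared using co-variate analysis and student's T-test or Mann-Whitney U-test", the choice between these two depending on whether the data are parametric. It adds a multivariable linear regression of binary outcomes on treatment with covariate adjustment, and the Abstract promises both univariate and multivariate analyses. No covariate is named, and the section does not say whether the unadjusted or the adjusted result governs. Non-union, the primary outcome, is not explicitly assigned to any one of these tests.

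**The concern.** When arms are balanced within hospital, differences between hospitals largely cancel out of the treatment contrast. A test that ignores hospital still counts those differences as noise. Its standard error is then larger than the real sampling variation, so p-values tend to be too large, and the balance bought by the allocation is not turned into precision. The chi-squared, t- and Mann-Whitney tests have no place for a hospital term, so as written they do not match the allocation scheme. What is at stake is some power, not a raised false-positive rate.

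**Working it through.** **Inputs from the article.** 21 hospitals; 175 patients per arm, 350 in total; 12% drop-out; nominal power 80%; type I error 5%, taken here as two-sided. Hence:

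- evaluable per arm: 175 × 0.88 = 154, or 308 in total
- average per hospital: 350/21 = 16.7 randomised, 308/21 = 14.7 evaluable

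**The plan's own figure.** The 175 per arm cannot be reproduced or refuted, because only a 15 percent difference is given and not the two arm rates. Nothing below depends on it beyond the 154 per arm.

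**Assumed.** The share of outcome variance lying between hospitals (ICC) is not in the article; 0 to 0.20 is shown.

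**Continuous score.** Assume perfect balance within hospital and a hospital effect common to both arms. With total variance set to 1:

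- standard error used by the unadjusted test: sqrt(2/154)
- actual standard error: sqrt(2(1 − ICC)/154)
- ratio, actual to used: r = sqrt(1 − ICC)

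For a score with 80% nominal power:

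- true type I error, unadjusted: 2[1 − Φ(1.960/r)]
- power, unadjusted: Φ(0.842/r)
- power with hospital in the model: Φ(2.802/r − 1.960)

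| ICC | r | Type I error | Power, unadjusted | Power, adjusted | Loss (points) |
|---|---|---|---|---|---|
| 0 | 1.000 | 5.0% | 80.0% | 80.0% | 0 |
| 0.02 | 0.990 | 4.8% | 80.2% | 80.8% | 0.6 |
| 0.05 | 0.975 | 4.4% | 80.6% | 82.0% | 1.4 |
| 0.10 | 0.949 | 3.9% | 81.2% | 84.0% | 2.7 |
| 0.20 | 0.894 | 2.8% | 82.7% | 87.9% | 5.3 |

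Losses come from unrounded powers; subtracting the rounded columns gives 2.8 and 5.2 in the last two rows.

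**Binary outcome.** The closed form above does not carry over to a low-rate binary outcome, so this was simulated: 21 hospitals of unequal size, about 308 evaluable patients, alternating allocation within hospital, a logit-normal hospital effect, and 10,000 runs per cell. The rates are assumed: 10% in both arms for type I error, 15% v 5% for power. Chi-squared ignoring hospital is compared with Cochran-Mantel-Haenszel stratified by hospital.

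| Latent ICC | Type I, chi-squared | Type I, stratified | Power, chi-squared | Power, stratified |
|---|---|---|---|---|
| 0 | 4.8% | 4.7% | 85.8% | 85.3% |
| 0.02 | 4.9% | 4.9% | 85.9% | 85.5% |
| 0.05 | 4.8% | 4.8% | 85.6% | 85.5% |
| 0.10 | 4.6% | 4.9% | 85.3% | 85.8% |
| 0.20 | 4.3% | 5.0% | 85.6% | 86.7% |

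Simulation error is about 0.2 points for type I error and 0.35 points for each power, so up to ICC 0.10 the two tests are practically level. At 0.20 stratifying gains 86.7 − 85.6 = 1.1 points.

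**Number of events.** At the same assumed rates, 0.15 × 154 + 0.05 × 154 = 30.8 non-unions, or about 1.5 per hospital. That is too few to support 20 hospital indicators in a model for non-union.

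**The case against.** The strongest reply is that adjustment is already planned. Statistical analysis mentions covariate analysis and an adjusted regression, the covariates are unnamed, and such a list is commonly left to an analysis plan that is not shown here. This stands in part: a reader might infer that hospital is excluded from every analysis, and the article does not say so. But the chi-squared sentence carries no mention of covariates, and nothing gives the adjusted analyses precedence over the unadjusted tests.

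A second reply is that the effect needs real differences between hospitals, which the article neither quantifies nor establishes. That stands. Two features that might be cited as evidence are weaker than they look:

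- Outcome measures says that dynamometer results are reproducible "especially when measured by one single examiner at each hospital". A reader might infer one examiner per site. The remark reports earlier reliability work, and Follow-up of patients allows a blinded researcher or other blinded qualified staff to do the tests. Comparison with the other arm would also cancel part of any examiner effect.
- The free choice of plate brand and the threshold for surgeon experience act only in the operated arm. They would make the treatment effect vary between hospitals, which is not the common hospital effect assumed above. If hospitals are regarded as a random sample, such variation makes the unadjusted standard error too small, not too large; a random intercept does not model it.

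A third reply is that minimisation reduces imbalance without removing it, and drop-out will disturb it further in hospitals of about 15 evaluable patients. This also stands: the figures for scores are approximate and lean towards the upper end.

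**Conclusion.** The mismatch between allocation and named tests is real, and its consequence is small. For continuous scores, at an assumed ICC of 0.02 to 0.10 with near-perfect balance and a common hospital effect, the true type I error is about 4.8% to 3.9% and about 0.6 to 2.7 points of power are lost. At ICC 0 nothing is lost. For non-union, at the assumed low rates, there is no material loss up to 0.10 and about 1 point at 0.20; the figures for scores must not be read across to the primary outcome.

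A reader might infer that the p-values are invalid or the false-positive rate raised. The calculation gives no support for that: in every case run, the type I error of the unadjusted test stays at or below 5%. This is a matter of precision and of matching the analysis to the design, not of validity.

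**What to change.** In Statistical analysis, state that the main between-arm comparisons account for hospital and for any other factor used in the minimisation. For binary outcomes (non-union, complications), use a Mantel-Haenszel test and a risk difference stratified by hospital. For scores (Constant, DASH, SF-36), use a regression with treatment and a hospital random intercept. Say that these take precedence over the unadjusted tests, which can remain as supporting analyses. Avoid 20 fixed hospital terms in the binary model, where events will be few.

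The cost is a sentence or two of text and slightly more analysis work. Hospital is known for every patient because allocation uses it, so no new data are needed. No material gain should be expected for non-union if hospitals differ little.

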### Study population

All patients with a dislocated midshaft clavicular fracture have to meet the following inclusion criteria before enrolment:

1. Fully displaced midshaft fracture (no fracture side contact of distal and proximal fragments) according to Robinson classification 2B1 and 2B2 (see Figure 1). The classification of the fracture will be confirmed on an anterior-posterior X-ray with a 30 degree caudocephalad view;

**Figure 1 F1:**
[figure not shown]
**Robinson Classification type 2 fractures**. Figure reprinted with permission of C.M. Robinson [39]. Right side of the figure shows type 2B1 and type 2B2 fractures.

2. Age between 18 and 60 years;

3. No medical contra-indications to general anaesthesia;

4. Signed informed consent by the patient or a legal representative;

If one of the following exclusion criteria applies, the patient is not eligible for the study:

1. Fracture in the proximal or distal third of the clavicle;

2. Pathologic fracture (bony abnormalities at the side of the fracture) or an open fracture;

3. Neurovascular injury of the shoulder region with objective neurological findings on physical examination;

4. Associated head injury (Glasgow Coma Scale < 12);

5. A significant ipsilateral upper extremity fracture, that would delay the functional recovery of the arm;

6. A midshaft clavicular fracture more than 14 days old at first hospital visit;

7. Inability to comply with follow-up;

8. Prior surgery to the shoulder or pre-existing shoulder complaints with subsequent loss of function;

### Interventions

For patients assigned to operative treatment, the procedure of applying the plate is performed according to standard procedures, including the position of the patient (beach chair position) and anaesthesia (i.e., general anaesthesia or interscalene nerve block or a combination of both). All patients admitted to the hospital for operative intervention receive antibiotic prophylactics (single dose) pre-operatively and after operation thromboprophylaxis is applied during the hospital stay (e.g., unfractionated heparin, Low Molecular Weight Heparin (LMWH), or equivalent). All operations are performed by skilled trauma surgeons, i.e. those who have performed more than five operations with a plate fixation, or by surgical residents under supervision of a skilled trauma surgeon. No restrictions are specified regarding the brand of plate fixation that will be used. Patients assigned to conservative therapy wear a sling for the first two weeks.

All patients, in both treatment arms, are advised to mobilise the shoulder functionally without weight bearing during the first six weeks. The exercise protocol consists of pendulum exercises up to functional movements without weight bearing in the first six weeks after trauma or operation. In the first two weeks pendulum exercises are started and more active exercise is initiated between two and four weeks postoperatively or after trauma. After six weeks, initial strengthening is started.

### Outcome measures

The primary outcome is the incidence of non-union. This is determined objectively on X-rays by an independent radiologist and two surgeons, and subjectively by evaluation of the clavicular and the arm function. The function of the arm is measured with the Constant Score. The Constant score consists of four variables, reflecting both function and pain of the shoulder joint [30,31]. The subjective variables in the Constant Score are pain, activities of daily living and arm positioning. The objective variables are range of motion (ROM) without pain and strength [32]. The arm strength is measured with the MicroFET2 (Micro Force, Evaluating and Testing 2, Hoggan Health Industries Inc, West Jordan, UT, USA), a hand-held dynamometer. This device measures the force a patient can produce against the force of the examiner in Newton (N). All arm movements (i.e., retroflexion, anteflexion, abduction, adduction, endorotation and exorotation) are evaluated six weeks after initial trauma or operation in comparison with the contralateral side and thereafter at each follow-up moment. For all measurements the Make Test is used. The Make Test is characterised by the examiner holding the dynamometer stationary while the subject exerts a maximal force against the dynamometer and the examiner [33]. The results produced with the hand-held dynamometer have been shown to be reproducible, especially when measured by one single examiner at each hospital (intra-rater reliability) [33]. The inter- and intra-rater reliability of hand-held dynamometry varied in the range from good to high [34,35].

Secondary outcomes are clinical function measured with the DASH Outcome Measure, pain scores, cosmetic aspects, quality of life and complications of the allocated treatment. The Disabilities of Arm, Shoulder and Hand (DASH) Outcome Measure is a validated 30-item, self-report questionnaire designed to describe the disability experienced by people with upper-limb disorders and to monitor changes in symptoms and function over time. The DASH Outcome Measure consists of two components: the disability/symptom section (30 items) and the optional high performance Sport/Music module (4 items). The questions involve the degree of difficulty in performing a variety of physical activities because of problems with the arm, shoulder, or hand. The severity of pain, activity-related pain, tingling, weakness and stiffness is investigated, as well as the effect of upper limb problems on social activities, work, sleep, and self-image [36,32,37]. The questionnaire is filled out at each follow-up moment.

Cosmetic aspects are included in the follow-up questionnaires. These questions are subjective and involve satisfaction with the appearance of the shoulder with and without surgery. The Health Related Quality of Life (HR-QOL) will be evaluated using the Short Form-36 (SF-36). The SF-36 is a validated survey on general health with 36 questions, representing eight health domains that are combined into a physical and a mental component scale [38]. The Physical Component Scale (PCS) contains the health domains physical functioning, role limitations due to physical health, bodily pain and general health perceptions. The Mental Component Scale (MCS) contains the health domains vitality, energy, fatigue, social functioning, role limitations due to emotional problems and general mental health. Scores ranging from 0 to 100 points are derived for each domain, with lower scores indicating poorer function. These scores will be converted in a norm-based score and compared with the norm values for the general population of the United States (1998), in which each scale was scored to have the same standardized average (50 points) and the same standard deviation (10 points) [32].

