At each hospital visit various intrinsic (patient-related) and injury-related variables are collected. As part of standard care, X-rays are taken at admission and each follow-up moment. The X-rays are performed in anterior-posterior view and 30° caudocephalad view. After two weeks an X-ray of the contralateral shoulder is taken for comparison with the affected shoulder. The DASH outcome measure and SF-36 are filled out by the patient after two weeks, six weeks, three months and one year. The Constant score of both shoulders is determined after six weeks. The Constant score of the affected shoulder is also determined after three months and one year. The functional tests are performed by a single-blinded researcher or other single-blinded qualified personnel. During these tests, the patients have a sticker on the affected shoulder and they are not allowed to tell the examiner which therapy they have undergone. Furthermore, at each visit the researcher collects medical information according to the follow-up list (i.e., complications/adverse events, secondary interventions). Serious adverse events will be reported directly.

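### The Constant Score and the DASH have different roles in the abstract and the main text, so the shoulder-function conclusion is not tied to one instrument in advance

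*Protocol article*

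**What the plan says.** Four places in the protocol article bear on how shoulder function is assessed.

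- **Abstract, Methods/design.** After non-union as primary: "Secondary outcome will be the functional outcome, measured using the Constant Score". The DASH is mentioned together with the SF-36 and has another status: "Disabilities of Arm, Shoulder and Hand (DASH) Outcome Measure will be monitored as subjective parameters".
- **Outcome measures, primary-outcome paragraph.** Non-union is determined on X-rays and also "subjectively by evaluation of the clavicular and the arm function". The next sentence names the instrument: "The function of the arm is measured with the Constant Score".
- **Outcome measures, secondary-outcome paragraph.** "Secondary outcomes are clinical function measured with the DASH Outcome Measure, pain scores, cosmetic aspects, quality of life and complications of the allocated treatment". The Constant Score is not in this list.
- **Statistical analysis.** Together with complication rates, "recovery of function of the shoulder will be compared between the two intervention groups using the Chi-squared test". No instrument is named. All remaining endpoints go to a covariate analysis and a t-test or Mann-Whitney test, and significance is declared below 0.05.

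Follow-up of patients schedules both instruments: the DASH at two weeks, six weeks, three months and one year, and the Constant Score of the affected shoulder at six weeks, three months and one year. It adds "The functional tests are performed by a single-blinded researcher or other single-blinded qualified personnel".

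**The concern.** The stated aim has two parts, fracture consolidation and shoulder function. For the second part, the article gives two different answers to the question of which instrument is the secondary functional outcome, and the analysis section does not decide between them. Someone writing the results could cite the abstract for the Constant Score or the main text for the DASH, and either would appear to be pre-specified. If the two instruments disagree, the choice between them could be made with the results in view.

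The instruments can disagree because they measure partly different things. The Constant Score includes range of motion and dynamometer strength. The DASH is a self-report questionnaire on symptoms and activities, and it starts one visit earlier.

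**Working it through.** **Step 1: the passages side by side.**

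| Place | Constant Score | DASH |
|---|---|---|
| Abstract, Methods/design | the secondary functional outcome | monitored subjective parameter |
| Outcome measures, primary paragraph | measures the arm function used in determining non-union | not mentioned |
| Outcome measures, secondary paragraph | not listed | the secondary functional outcome |
| Statistical analysis | not named | not named |

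Each instrument has a different role in the abstract and in the main text. No sentence ranks them or says which one carries the functional conclusion.

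**Step 2: is this only a shortened abstract?** A shortened abstract would list fewer of the same secondary outcomes. Here the abstract labels as secondary an instrument that the main list lacks, and gives the main list's functional instrument a different label. The two statements differ in substance.

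**Step 3: is there a stated figure to reproduce?** No. The sample size section (175 per group, 350 in total) is based on non-union only. It neither supports this point nor is affected by it.

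**Step 4: illustration of what an open choice costs.** Inputs: a 0.05 threshold per test (Statistical analysis; sidedness is not stated, two-sided assumed), two instruments, no true difference on either, and test statistics that are bivariate normal with correlation r. The documents give no r, so a range is shown.

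P(at least one rejects) = 0.05 + 0.05 − P(both reject)

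- r = 0: 0.10 − 0.05² = 0.0975
- r = 0.5: 0.10 − 0.0093 = 0.0907
- r = 0.7: 0.10 − 0.0165 = 0.0835
- r = 0.8: 0.10 − 0.0219 = 0.0781
- r = 0.9: 0.10 − 0.0296 = 0.0704

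With one instrument named in advance, the figure is 0.05. These probabilities count a false difference in either direction. The chance of a false result favouring one given arm is about half: 4.5%, 4.2% and 3.9% at r = 0.5, 0.7 and 0.8, against 2.5% with a single instrument.

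**The case against.** The strongest case on the other side has four parts.

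1. **The mismatch is a by-product of the primary-outcome paragraph.** The secondary list lacks the Constant Score because the Constant Score has been placed under non-union. Settle that paragraph and the Constant Score becomes an ordinary secondary outcome. Much of this stands, and the fix must therefore include that paragraph. It does not remove the point: with non-union defined on X-rays alone, the main text would still name only the DASH as the functional secondary outcome, and the abstract only the Constant Score.

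2. **Ranking secondary outcomes belongs to the full protocol or the analysis plan.** A missing ranking would not be a finding. Two published statements that disagree are a different matter, because an analysis plan could follow either and claim agreement with the article.

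3. **Both instruments are disclosed and scheduled, and the primary outcome is unaffected.** This is correct and limits the weight of the point. Neither instrument could be introduced after the fact. What remains open is which of them is presented as the functional result.

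4. **The contrast between the instruments is easily overdrawn.** A reader might infer a choice between a blinded measure and an unblinded one, and that the DASH result would be biased. The documents do not support this. The abstract says nothing about blinding. The Follow-up section blinds the examiner, not the patient, and the article itself says "The subjective variables in the Constant Score are pain, activities of daily living and arm positioning". Strength is also what the patient chooses to exert. The difference is one of degree. No figure for bias in the DASH can be taken from the documents, and any such bias would exist whichever wording is adopted.

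**Conclusion.** The contradiction holds. The abstract, the two paragraphs of Outcome measures and the Statistical analysis section do not give the two instruments consistent roles, and the functional conclusion can be attached to either after the data are seen. This concerns a secondary outcome. It should be corrected because function is part of the trial's aim and correction is nearly free.

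The size is illustrative: 7.8% to 9.1% instead of 5%, for assumed correlations of 0.8 down to 0.5, two-sided tests and a free choice between them. A reader might take this as the chance of a false benefit of plate fixation. It is not, since it counts differences in either direction; for one given arm it is about 3.9% to 4.5%.

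Two further inferences go too far. The main text does not drop the Constant Score; it moves it into the primary-outcome paragraph. Nor do the documents make the abstract's choice the right one: nothing gives the abstract precedence, and either instrument could serve if it is chosen in advance and stated consistently.

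**What to change.** - **Abstract and Outcome measures (both paragraphs).** Give each instrument one role. List the Constant Score as a secondary functional outcome, separate from the determination of non-union, and the DASH beside it as the patient-reported functional outcome.
- **Functional conclusion.** State, before outcome data are seen, which instrument and which time point carry it. The abstract's choice, the Constant Score of the affected shoulder with a blinded examiner, at one year, is one consistent option. The other instrument is then supportive.
- **Statistical analysis.** Replace the unnamed shoulder-recovery endpoint with the chosen instrument, and compare it as a numeric score using the covariate analysis, t-test or Mann-Whitney test already planned. Take it out of the Chi-squared sentence: putting the instrument's name there would place a numeric score under a test for categories with no cut-off.

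The cost is wording in the abstract and two sections. Both instruments are already collected at one year, so no visit, measurement or sample size changes. The downside is that a difference seen only on the other instrument is reported as supportive and not as the main functional result.
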